### Participants

Following the protocol of the Research on Obesity and Diabetes among African Migrants (RODAM) study, which focused on obesity and type 2 diabetes among African migrants (44), this study estimates the prevalence of undiagnosed type 2 diabetes (T2D) in the Cape Coast metropolis of Ghana, at 6-7%, and the prevalence of obesity at 17%. The study aims for a power of 0.90 with α=0.05, including the Bonferroni correction. Using these parameters, a sample size of approximately 1000 would be sufficient to detect a 10% proportion of undiagnosed T2D. In order to compensate for attrition, the study seeks to recruit 1200 self-identified healthy individuals from 13 urban and rural communities in the Cape Coast Metropolis, who have not been previously diagnosed of diabetes or prediabetes prior to the study for collection of baseline data.

Due to the large and geographically dispersed population, a multistage sampling technique would be employed to sample participants for this study. This will be done in three stages, where the first stage involves dividing the population into clusters, based on the already existing communities within the metropolis. The second stage involves sampling these clusters to be used in the study by using systematic random sampling. At this stage, 13 clusters representing 13 rural, peri-urban and urban communities would be selected for the subsequent sampling stage. Finally, the third stage would involve further sampling within each selected cluster to randomly select households, and recruit the first two persons from each family line (with random replacement) in the indigenous communities, while using convenience sampling in non-indigenous communities. It is envisaged that approximately 90-100 participants will be randomly selected from three rural communities (Efutu Mampong, and Efutu), four fishing communities (Abekam, Duakor, Ekon, and Ntsen), three peri-urban communities (Ayeko-Ayeko, Ankaful and Nkanfoa) and one urban community (UCC), two market communities (Kotokuraba and Abura Markets), and one artisanal community (Siwdu). Household mapping will be done utilizing the 2021 Housing Census Data. All the 1200 volunteers will be recruited from their communities of origin before disclosing any monetary benefits.

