### Biochemical measurements

#### Fasting blood collection and processing

Eligibility for participating in the OGTT requires participants to fast for at least eight hours, with permission to drink plenty of water from 8pm the night before sample collection. Medical Laboratory Scientists licensed by the Allied Health Profession Council of Ghana will collect the blood specimen using standard venipuncture techniques, with a vacuum blood collection system. Fasting blood specimen of 3ml is collected into one gel separator tube and 2ml each of fasting blood is collected into separate fluoride oxalate tubes for HbA1C and FPG analysis. The blood specimens are kept on ice and transported to the lab for processing and storage. An initial fasting blood glucose test is performed using an Accu-Chek Instant meter and Accu-Chek Instant test strip (Roche, Germany, 2019) to determine glucose tolerance levels and the safety of the participants before subsequent glucose administration for the OGTT procedure. Blood specimen for the other biochemical measurements in this study are also collected in the gel separator tube. These specimens are separated at 3000rpm for 3 minutes and the serum aliquoted into Eppendorf tubes for blood chemistry analysis, immunoassay analysis and storage for reference. For the specimen in the two fluoride oxalate tubes, one is separated and the plasma is aliquoted into Eppendorf tubes and used for fasting blood glucose analysis, whereas the other fluoride oxalate tube sample is used for HbA1c analysis.

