### Data analysis

For the accuracy of data and information, data collected through the Kobo Collect toolbox application will be downloaded into an Excel spreadsheet and screened visually and statistically. Data will be analyzed and interpreted by the principal investigator and his local collaborators and shared back with foreign collaborators. In the attempt to make the findings of the study public, data analysis will be conducted using STATA 16 and SPSS 23. Statistical tools specific and relevant to the research questions and hypotheses of the CarMeR study would be used. To determine the prevalence of undiagnosed diabetes, prediabetes and other associated cardiovascular risks, data on OGTT, FPG and HbA1c will be analyzed using descriptive statistics (percentages and confidence intervals). In order to investigate the differences in phenotype, diabetes, prediabetes, and normoglycemic groups will be compared based on BMI and body composition (waist hip ratio, body fat percentage, skeletal muscle, total body water) using analysis of variance (ANOVA) and t-test. To profile the ocular characteristics and complications of the diabetes and prediabetes groups, a cross-tabulation and a subsequent chi-square test will be done to assess the association between glycemic dysregulation and the presence of ocular complications (diabetic retinopathy, cataract, macular edema). For the purpose of ascertaining whether the predominant etiological factor of undiagnosed diabetes in this populations is insulin resistance or beta-cell failure, a homeostasis model analysis of beta [HOMA-β and HOMA-IR] will be computed and logistic regression will be used to determine the dominant factor. As a way of determining the sensitivity of other diagnostic alternatives (FPG and HbA1c) in comparison to the multi-sampled OGTT, receiver-operated characteristics (ROC curves), including sensitivity and specificity curves, will be used. Finally, to ascertain whether lifestyle changes (food choice, physical activity, weight loss, psychosocial counseling) over a one-year period impacts biomarkers of glucose regulation, a linear mixed model regression analysis, controlled for baseline characteristics will be used. T-tests will be conducted to observe changes in glucose regulation biomarkers.

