To manage missing data, imputation and deletion methods would be employed. When the percentage of the missing data is low and not across all observations, the imputation method would be used to estimate the missing data. However, where the number of missing data points is high or the entire data point is missing information, the data point would be deleted during analysis to reduce bias.

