The study anticipates some challenges in the execution of this study. The geographical tapestry in the area of interest provides a challenge in reaching the rural communities for the sample collection. To address this, the research team will collaborate with the local gatekeepers to facilitate access and encourage participation. Additionally, cultural dispositions pose challenges, as some community members may prefer not to know their cardiometabolic status, and may not allow their samples to collected. To remedy this, there will be extensive community engagement and campaigns to raise awareness about the importance of the study and its potential health benefits. Another possible challenge could be participants refusing to continue with the study and further sample collection, due to discomfort associated with blood draws. To mitigate this, the study intends to adopt strategies that will minimize discomfort remarkably, such as using experienced phlebotomists, explaining all procedures clearly, and offering support and reassurance to the participants for the entire duration of the study.

Despite these anticipated challenges, it is believed that the robust methods used in the study will facilitate obtaining reliable and valid results. The study results will be released when both phases of the study have been completed.

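### The missing-data rule deletes data where much is missing and claims that this reduces bias; deletion is at best neutral, and can bias the prevalence and one-year estimates in either direction

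*Protocol article*

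**What the plan says.** The rule closes the Data analysis section of the protocol article and has two branches.

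- Little missing: "When the percentage of the missing data is low and not across all observations, the imputation method would be used to estimate the missing data".
- Much missing: "where the number of missing data points is high or the entire data point is missing information", in which case "the data point would be deleted during analysis to reduce bias".

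No cut-off separates low from high, and no missingness assumption is stated. The term *data point* is used both for something that is counted when missing and for something that can be wholly empty, so it may mean a value, a visit record or a participant.

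The same section fixes the analyses that the rule would act on. For prevalence, "data on OGTT, FPG and HbA1c will be analyzed using descriptive statistics (percentages and confidence intervals". For the one-year lifestyle phase, "a linear mixed model regression analysis, controlled for baseline characteristics will be used", together with t-tests.

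The Discussion anticipates two sources of missing samples: people who would rather not learn their cardiometabolic status, and "participants refusing to continue with the study and further sample collection, due to discomfort associated with blood draws".

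**The concern.** The protocol commits to a rule here and gives a reason for it, so this is not a detail left to an analysis plan. The reason is incorrect. Deleting incomplete data removes no bias. It does no harm when the loss is unrelated to outcome. When the loss is related to outcome, it turns the estimate into one about the people who remained, and the discrepancy tends to grow with the fraction lost. The rule reserves deletion for exactly that situation.

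The protocol's own expectations make outcome-related loss plausible. Someone who does not want to know their status may suspect that it is abnormal. Over a year of lifestyle change, people who are doing badly may be likelier to stop.

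There is also a tension within the section. A likelihood-based mixed model can use every visit that was observed. If *data point* means a participant or a partly observed record, the deletion rule throws away earlier visits that the planned model could have used.

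**Working it through.** The plan states no figure for missingness, so there is none to reproduce. The calculations below show what the deletion rule can do under stated assumptions.

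**Prevalence**

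Inputs: true prevalence p = 6.5%, the middle of the 6–7% expected under Participants. Overall loss m = 16.7%, the loss implied if 1200 is 1000/(1 − m), since 1 − 1000/1200 = 0.167. The protocol does not state an attrition rate, so this reading is an assumption. The share of cases lost, m_D, is also an assumption and is varied.

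Prevalence among complete records = p(1 − m_D)/(1 − m), with 1 − m = 0.833.

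| Share of cases lost | Calculation | Reported prevalence |
|---|---|---|
| 30% | 0.065 × 0.70 / 0.833 | 5.5% |
| 25% | 0.065 × 0.75 / 0.833 | 5.9% |
| 16.7% (unrelated to disease) | 0.065 × 0.833 / 0.833 | 6.5% |
| 10% | 0.065 × 0.90 / 0.833 | 7.0% |
| 5% | 0.065 × 0.95 / 0.833 | 7.4% |

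Deletion is neutral only in the middle row, and the error can go either way.

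**One-year change and reversal**

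All inputs are assumptions. Changes at 6 and 12 months are standard normal with true mean 0 and correlation 0.64. Reversal means a 12-month change in the best 30% of the true distribution. The log-odds of dropping out after month 6 rise linearly with a worse 6-month change, by b per SD, with the intercept set to give the stated dropout. Among completers, the mean 12-month change is 0.64 times the mean 6-month change.

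| Dropout | b | Completers' mean 6-month change | Completers' mean 12-month change | Completers' reversal (true 30%) |
|---|---|---|---|---|
| 16.7% | 0.5 | −0.08 SD | −0.05 SD | 32% |
| 16.7% | 1.0 | −0.15 SD | −0.09 SD | 33% |
| 30% | 0.5 | −0.14 SD | −0.09 SD | 33% |
| 30% | 1.0 | −0.25 SD | −0.16 SD | 35% |

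For example, 0.64 × (−0.25) = −0.16. Negative values are improvement, so all of it is spurious. Because dropout depends only on an observed value, a likelihood analysis of all visits recovers the true mean of 0.

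**A second mechanism, as a check on size**

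This simulation had three visits, n = 300, 2000 runs, correlations of 0.5 to 0.7, a true 12-month mean and true change of −0.50 SD, and 31% dropout depending on the mid-study level rather than the mid-study change. Deleting incomplete participants gave a month-12 mean of −0.71 SD (0.21 SD too low) but a change of −0.53 SD (0.03 SD too favourable). Likelihood estimation on all available data gave −0.50 SD for both. The size of the bias therefore depends strongly on the mechanism and on which quantity is reported.

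**The case against.** Several points in the plan's favour stand.

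- **Imputing when little is missing is not an error**, and a wholly empty record cannot usefully be imputed. A reader might infer that the whole rule is upside down. Only the deletion of partly observed data and its stated justification are at fault.
- **The text does not say that participants are deleted.** If *data point* means a visit record, dropping an empty visit is what a mixed model on observed visits does anyway, and nothing under Data analysis restricts that model to completers. The participant reading is possible but not established.
- **Bias is conditional and its direction is not fixed.** The Discussion gives reasons for refusal but no size or direction. A reader might infer that both errors flatter the study. The documents do not support this: the Introduction is built on high undiagnosed prevalence, so under-reporting would work against it.
- **The glucose-drink safety check is weak evidence of lost cases.** The fasting meter test is done "to determine glucose tolerance levels and the safety of the participants before subsequent glucose administration for the OGTT procedure", and a reader might infer that the highest-glucose people get no OGTT and disappear from the prevalence. No rule for withholding the OGTT is stated. These people would have fasting samples, and the Diagnoses section accepts FPG or HbA1c as well as the 2-hour OGTT. If 10 or 20 of 1200 were affected (0.8% or 1.7%), the rule would most naturally impute. An OGTT-only figure, which the first objective could be read to imply, might still be affected.
- **The one-year figures rest on assumed dropout.** The only hint of attrition, 1000 raised to 1200, concerns the survey. Reversal is a stated objective, but the described analysis is of biomarkers.

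These points limit the size and certainty of the concern. None makes the stated justification correct.

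**Conclusion.** The point holds in a limited form. Giving bias reduction as the reason for deleting data where much is missing is wrong, and the rule leaves its unit and threshold undefined. Where missingness relates to outcome, which the Discussion makes plausible but does not establish, the prevalence and one-year estimates can be biased in either direction.

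Under the stated assumptions, prevalence moves by roughly one percentage point either way around 6.5%. One-year change among completers is off by about 0.05–0.16 SD, and reversal by about 2 to 5 percentage points, for dropout of 17% to 30%. The second mechanism gave as little as 0.03 SD for change. These are within-group figures; the error in a between-arm comparison would depend on how dropout differed between arms. The loss of usable earlier visits follows only if *data point* means a participant or a partly observed record.

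The rule should be changed before analysis, because the correction is cheap and the planned model already supports a better approach.

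**What to change.** Replace the missing-data paragraph under Data analysis:

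1. Remove the deletion rule for partly observed participants and the claim that it reduces bias. Define the unit, and let only wholly empty records drop out.
2. Fit the mixed model to all observed visits of every enrolled person, under a stated missing-at-random assumption.
3. Use multiple imputation for partly observed data in the prevalence, regression and reversal analyses, including age, sex, community, BMI and the available glucose measures.
4. Keep participants without a full OGTT in the prevalence denominator, classified from FPG or HbA1c as the Diagnoses section already allows, or imputed.
5. Add a sensitivity analysis that counts dropouts as not reverted.

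The cost is a few sentences of analysis text and modest programming. No additional data are needed.

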### Data management

A casebook will be created for each participant and numbered from UCC0001-UCC1200 based on the sample size of the study. All printed information about the participant is stored in a metal cabinet at the PI’s office with only the PI and the Co-PI having access to the keys. In the case of a future collaboration or requests to use the data collected, participants’ bioinformation will be removed before the data is shared. All sera and plasma would be stored in a freezer at -40C in the CERL for future research and collaboration, with samples being stored for up to 10 years. Leftover blood will be disposed of in two main ways. The first is incineration, where the leftover unused blood samples are sent to the University of Cape Coast Hospital for incineration. The second is decontamination and disposal by adding 0.5% chlorine to the leftover blood for 10 minutes to decontaminate, after which it is deemed safe for the environment, hence, are disposed-off through flushing into covered gutters.

### Ethical considerations

Ethical clearance for the study has been obtained from Institutional Review Board (IRB) of University of Cape Coast (UCC), Ghana. The anticipated potential risks of this are fatigue associated with answering the questionnaire, the discomfort associated with Intra-Venous (IV) insertion, and the drinking of the glucose solution. As a result, a medical practitioner would be present at the study sites at all the times to initially evaluate the participants and oversee IV insertions and blood draws. Qualified and registered phlebotomists/laboratory scientists will perform the IV insertions and blood draws. All discomforts and benefits associated with the entire study would be explained to the participants in their preferred languages, having being assured of confidentiality before written informed consent is obtained for participation in each part of the study (survey, anthropometric body and vital signs measurements, biochemical measures, eye examination). Participants are also made aware of the tests being performed with the collected samples [FBG, glycated hemoglobin (HbA1c), homocysteine, high-sensitive C-reactive protein (hsCRP), lipid panels (serum cholesterol, plasma HDL, LDL, TG), creatinine, liver function tests (AST, ALT), total protein for kidney function] and the amount of blood to be drawn at each time. All participants are counseled on the possibility of being diagnosed with diabetes or prediabetes, how it would affect their lives, and possible solutions. Participants are given the opportunity to withdraw from the study at any time they feel discomfort. Data collected, including participants’ bioinformation are kept in a secure cabinet, accessible only by the PI and the Co-PI. All COVID-19 protocols would be in place to protect both the researchers and participants. All participants who agree to and complete the first part of the study are remunerated.

### Expected outcomes

The CarMeR study is expected to help provide insights on the burden and possible management of diabetes, prediabetes and related cardiometabolic complications in a typical African population. It will ascertain the prevalence of undiagnosed diabetes and prediabetes, as well as explore the relationship between these diseases and cardiovascular risks such as obesity, dietary habits, socioeconomic status, stress, sleep pattern and location. Furthermore, it will provide a nuanced understanding of the phenotypic and biochemical characteristics of the people with diabetes and prediabetes, with a focus on body composition, insulin resistance, and beta-cell function. The study will also describe the ocular characteristics of the participants, in order to identify the ocular complications associated with abnormal glucose tolerance. In the subsequent phase of the study, the efficacy of lifestyle interventions like diet, physical activity, and psychosocial counseling in preventing or reversing diabetes and prediabetes, will be assessed.

## Discussion

Empirical evidence has shown that non-communicable diseases (NCDs), which persist over time, have now emerged as a significant public health challenge worldwide, owing to their alignment with infectious diseases (45, 46, 63). According to the World Health Organization profiles of NCDs, NCDs claim the lives of 41 million individuals annually, accounting for approximately 71% of deaths globally (64). Despite the historically higher prevalence of NCDs in developed nations, a growing concern lies in the fact that they are now common in low-and middle-income countries (LMICs) such as Ghana (65). Cardiometabolic diseases (CMDs) are a group of NCDS, mainly diabetes, coronary heart disease (CHD), and stroke, which are rapidly increasing in prevalence, particularly in LMICs (4, 66–68). Between 2007 and 2017, mortality associated with diabetes, coronary heart disease (CHD), and stroke increased dramatically by 34.7%, 22.3%, and 16.6%, respectively (69). Lifestyle changes remain an essential modifiable factor influencing the risk of mortality in people living with CMDs (29). Previous studies have established a significant relationship between adherence to a healthy lifestyle, including abstinence from smoking, regular physical activity, a balanced diet, and a reduced risk of mortality from CMDs (70–72). It is worth noting that these lifestyle risk factors of severe tobacco use, physical inactivity, and a lack of a balanced diet usually co-occur, making individuals not only susceptible to one type of CMD, but also to all of them. However, there is a paucity of data on the degree to which a combination of lifestyle factors affects the risk of mortality in individuals with CMDs, especially in an African-born population. Given the increasing prevalence of CMDs and consequent increase in mortality, it is essential that there is substantial public health research and promotion of health through culturally sensitive interventions that enable a comprehensive healthy lifestyle (73).

Previous studies (2, 73) have attempted to investigate the risk factors associated with CMDs in Ghana. However, no study has comprehensively explored how demographic characteristics, physical activity and biochemical measures affect the development and progression of CMDs. Certain Ghanaian studies have attempted to explore these possible risk factors, but have done so in isolation and did not account for the influence of other potent factors on the development and progression of CMDs. One study (2) assesses CMDs and their effects on specific organ damage with another (73) mostly focusing on CVDs more than metabolic diseases like diabetes. Understanding the complex interplay of risk factors that lead the genesis and progression of CMDs is essential, especially in the African context. Embracing a multidisciplinary approach that facilitates a more comprehensive evaluation of CMDs development is key to identifying and attempting to remedy the risk factors that predisposes individuals to CMDs (4). Thus, the CarMeR study sought to investigate the risk factors associated with diabetes and one of the most debilitating cardiometabolic diseases in Ghana.

The strength of the CarMeR study is in the incorporation of all three steps of the WHO STEPwise approach (74). As recommended by the World Health Organization, the CarMeR Study utilized all steps to assess risk factors. These steps included the first step being a questionnaire-based assessment, the second step being physical measurements, and the third step being biochemical measures. This reflects the methods of previous studies that have adopted and endorsed the WHO STEPwise approach as an effective NCD surveillance tool (38, 39, 46). The three distinct steps of the WHO STEPwise approach offer a comprehensive approach to understanding risk factors, which is essential for effective intervention and preventive measures.

The CarMeR study is unique because it includes a comprehensive assessment of socio-demographic factors, psychological and behavioral factors, genetic factors and visual factors, complemented by an accurate measure of lifestyle behaviors such as physical activity, and a thorough examination of biochemical parameters of CMDs. With a substantial sample size of 1,200, the utilization of a standard NCD risk factor investigation approach such as the WHO STEPwise approach, and the meticulous application of the biopsychosocial model, the CarMeR study is strategically positioned to determine and subsequently modify the primary risk factors for CMDs within the Ghanaian population.

This study’s conceptual model is based on the biopsychosocial model, which acknowledges the multifactorial nature of CMDs development. Given the marked demographic variations within the Ghanaian population, it is important to investigate how prominent disease determinants such as genetic predisposition, socioeconomic status, family history, occupational influences, early life experiences, lifestyle choices, ethnicity, religion, sleep patterns, and stress levels affect the development of CMDs such as diabetes in an African-born population. The primary objective of this research and future studies from CERL is to provide valuable insights into the prevalence of cardiometabolic diseases and their associated risk factors in Ghana and African-born populations. The findings of this study have the potential to develop and improve interventions for individuals at risk for cardiometabolic diseases within the African context. The CarMeR study promises a positive impact on people affected by cardiometabolic diseases by providing culturally sensitive and adaptable lifestyle interventions. The participants in this study can utilize the results to gain a better understanding of their health status and effectively integrate lifestyle modifications into their daily lives, which can be pivotal in reducing the cardiometabolic disease burden in Ghana and Africa. Furthermore, the prospective results from the CarMeR study hold unlimited potential to uncover previously unexplored pathways in cardiometabolic health, offering opportunities for improved diagnosis and management of cardiometabolic diseases.

The study anticipates some challenges in the execution of this study. The geographical tapestry in the area of interest provides a challenge in reaching the rural communities for the sample collection. To address this, the research team will collaborate with the local gatekeepers to facilitate access and encourage participation. Additionally, cultural dispositions pose challenges, as some community members may prefer not to know their cardiometabolic status, and may not allow their samples to collected. To remedy this, there will be extensive community engagement and campaigns to raise awareness about the importance of the study and its potential health benefits. Another possible challenge could be participants refusing to continue with the study and further sample collection, due to discomfort associated with blood draws. To mitigate this, the study intends to adopt strategies that will minimize discomfort remarkably, such as using experienced phlebotomists, explaining all procedures clearly, and offering support and reassurance to the participants for the entire duration of the study.

Despite these anticipated challenges, it is believed that the robust methods used in the study will facilitate obtaining reliable and valid results. The study results will be released when both phases of the study have been completed.

